### Blinding

Operators and care providers will not be blinded, and the outcome assessors and data analysts will be blinded to the intervention. Decisions regarding ongoing treatments will be made according to every unit’s guidelines and clinical practice. The authors had two meetings before the study to obtain consensus for neonatal care.

### Sample size calculation

The proposed sample size is calculated according to the incidence of BPD. According to previous reports and the average data from every unit involved in the trials [6, 7], approximately 60% of infants born at 25^+ 1^ to 27^+ 6^ gestational weeks and approximately 15% among those born at 28^+ 1^–31^+ 6^ gestational weeks have developed BPD during the past 5 years. The presumed incidence of BPD will be approximately 25% in the pooled population of our trial. Considering an alpha error rate of 0.05 and a power of 0.8 to detect an expected 20% reduction in the incidence of BPD, 258 infants will be enrolled in each group. To consider factors such as data incompleteness, failure to follow up, or early dropout, we plan to recruit 300 preterm neonates for each group.

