## Background

In the last several years, dramatic improvements have been made in the management of respiratory distress syndrome (RDS) in preterm infants, including early establishment of FRC by noninvasive respiratory support, early rescue instead of prophylactic surfactant use, and curtailed application of mechanical ventilation (MV). All these changes have greatly improved the outcome for babies with RDS [1, 2].

Less invasive surfactant administration (LISA), as an innovative mode of surfactant delivery, is getting increasing attention in the management of preterm infants with RDS. This technique is characterized by the use of a thin catheter to deliver surfactant instead of an endotracheal tube and by keeping continuous positive airway pressure (CPAP) support during the course of administration [3]. A recent systemic review and meta-analysis in preterm infants with RDS indicated that surfactant administration via the LISA method decreased the combination rate of mortality or bronchopulmonary dysplasia (BPD) and reduced need for MV during the first 72 h of life [4]. However, the implementation of the technique requires an experienced clinician and consistence when performing the procedure. Moreover, the mechanisms underlying the beneficial effect of LISA over conventional methods are not fully understood, and further research is warranted [5]. While the intubation-surfactant-extubation (INSURE) technique as a conventional method has been widely used, evidence on superiority, efficacy, and safety of the LISA method over conventional surfactant administration are needed.

To provide more evidences and elucidate the potential protective mechanisms of the LISA method, we therefore conduct a multicenter, prospective, randomized controlled trial in China. This trial aims to compare the effects of the LISA method with those of endotracheal surfactant administration immediately followed by positive pressure ventilation with a designated lower peak pressure than it does in INSURE (LPPSA) in preterm infants with RDS and indicated for surfactant administration. Our hypothesis is that the effects of designated low positive pressure ventilation use following conventional surfactant administration (LPPSA) are not inferior to LISA in the treatment of preterm infants with RDS.

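### The 80% power for BPD is claimed for a reduction assigned to neither arm, although the hypothesis expects LPPSA to do no worse than LISA

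*Protocol article*

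**What the plan says.** Under Sample size calculation, BPD is the sizing endpoint: "The proposed sample size is calculated according to the incidence of BPD". The rates come from two kinds of source, "According to previous reports and the average data from every unit involved in the trials", and cover infants in two gestational-age bands who "gestational weeks have developed BPD during the past 5 years" preceding the trial. They are pooled into one figure: "The presumed incidence of BPD will be approximately 25% in the pooled population of our trial". The requirement is then set: "Considering an alpha error rate of 0.05 and a power of 0.8", "to detect an expected 20% reduction in the incidence of BPD". The result is 258 infants per group, raised to 300 for losses. The paragraph does not assign the 25% or the reduction to an arm, and does not say whether the 20% is relative or absolute or whether alpha is one- or two-sided.

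Other sections define what is compared:

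- **Grouping:** there are two arms, LISA and LPPSA. LPPSA follows the INSURE procedure with a lower designated peak pressure.
- **Abstract, Discussion:** LISA is thought to work chiefly by sparing the lung high-pressure ventilation just after surfactant.
- **Background:** the hypothesis is that LPPSA is not inferior to LISA. The article gives no margin.
- **Statistical methods:** the arms are compared by t-test, chi-squared test and regression models, with P < 0.05 as the criterion.

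**The concern.** A power statement belongs to a particular contrast between the randomised arms. Here the contrast is a pooled historical rate and a reduction from it, and neither is attached to LISA or LPPSA. If LPPSA also avoids high pressure, and that is the main reason LISA works, the two BPD rates should be close. The hypothesis says as much. The sizing nevertheless relies on a sizeable difference between them.

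The risk lies in how a null result is read. If the chi-squared test for BPD is not significant, the finding will appear to come from a trial with 80% power and may be taken as showing that LPPSA is as good as LISA. That is the conclusion the hypothesis looks for, and the stated power does not support it.

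**Working it through.** **Inputs from the Sample size calculation:** BPD rate 25%; reduction 20%; alpha 0.05; power 0.80; 258 per group, 300 with the loss allowance (1 − 258/300 = 14%). Allocation is 1:1 (Randomization). Alpha is taken as two-sided, which is an assumption.

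**Step 1: reproduce 258.** With p̄ = (p1 + p2)/2,

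n = [1.96·√(2p̄(1−p̄)) + 0.8416·√(p1(1−p1) + p2(1−p2))]² / (p1−p2)²

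- Relative reading, 25% versus 20%: (1.1575 + 0.4961)² / 0.05² = 1093.7, so 1094 per group (862 one-sided).
- Absolute reading, 25% versus 5%: (0.9897 + 0.4080)² / 0.20² = 48.8, so 49 per group.
- Solving for the rate that gives 258: 25% versus 15.13%, since (1.1101 + 0.4730)² / 0.0987² = 257.3. This is a relative reduction of about 39%.

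Neither reading of the 20% gives 258. The 15.1% is back-solved and does not appear in the article.

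**Step 2: power on the stated inputs, relative reading.**

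power = Φ{[|p1−p2|·√n − 1.96·√(2p̄(1−p̄))] / √(p1(1−p1) + p2(1−p2))}

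- n = 258: (0.8031 − 1.1575)/0.5895 = −0.601, power 27%.
- n = 300: (0.8660 − 1.1575)/0.5895 = −0.494, power 31%.

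One-sided, the figures are 39% and 43%. On the absolute reading, power exceeds 99%.

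**Step 3: power of the difference test as the LPPSA rate nears the LISA rate.** The article gives no BPD rate for either arm, so these rates are illustrative assumptions. LISA is set at 15%, close to the rate that reproduces 258.

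| LPPSA | LISA | Power, 258 per group | Power, 300 per group |
|---|---|---|---|
| 25% | 15% | 81% | 87% |
| 22% | 15% | 54% | 60% |
| 20% | 15% | 32% | 36% |
| 18% | 15% | 15% | 17% |
| 15% | 15% | 5% (type I error) | 5% |

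For 20% versus 15% at n = 258: (0.8031 − 1.0532)/0.5362 = −0.466, which gives 32%. With LISA at 20% instead, an LPPSA rate of 23% gives 13% (14% at 300).

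**Step 4: what 600 infants can deliver.** With equal rates p, the half-width of the 95% confidence interval for the difference is 1.96·√(2p(1−p)/n):

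| Rate in both arms | 258 per group | 300 per group |
|---|---|---|
| 15% | 6.2 points | 5.7 points |
| 20% | 6.9 points | 6.4 points |
| 25% | 7.5 points | 6.9 points |

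For scale, a 20% relative reduction from 25% is 5 points. With identical observed rates anywhere in this range, the interval would still include an excess of 5 points on LPPSA.

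**The case against.** The strongest reply is that historical unit data are an ordinary source for a planning rate, especially for a modified technique with no published rate to hand. That stands. The origin of the 25% is not in itself a fault; the fault is that neither the rate nor the reduction is tied to an arm, and that the assumed difference conflicts with the hypothesis.

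A second reply is that power falls as LPPSA succeeds only for a difference test, whereas under non-inferiority near-equal arms help. This also stands. With an assumed 10-point margin, one-sided 0.025 and LISA at 15.1%, power at 258 per group is about 3% if LPPSA is 25%, 33% at 20% and 89% at 15.1%. But the article states no margin, sizes the trial on a reduction and plans difference tests, so its 80% is not a non-inferiority power.

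Some stronger readings are tempting but not supported:

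- **That the 25% is an INSURE rate and so cannot apply to LPPSA.** The Background says that "the intubation-surfactant-extubation (INSURE) technique as a conventional method has been widely used", but this is a general remark. The Sample size calculation does not say how the past infants received surfactant, and it also draws on published reports.
- **That LPPSA is the control arm.** The article names no control. In its hypothesis LISA is the reference and LPPSA the tested technique.
- **That the eligibility criteria push the rate below 25%.** Excluding infants intubated in the delivery room may lower it. Requiring RDS with FiO2 of at least 0.3 and limiting birth weight to 600–1500 g may raise it. The net direction is unknown.
- **That 80% would be right against past care.** Step 2 shows that it is not on the relative reading, whatever the comparator.

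**Conclusion.** The concern holds in this limited form: the 80% power does not describe the LISA versus LPPSA comparison. The sizing assumes a BPD difference that the hypothesis does not expect, and the paragraph does not say which arm has which rate.

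On the stated inputs read as a relative reduction, two-sided, power is about 27% at 258 per group and 31% at 300. Under the contrast that does fit 258, power falls from about 80% towards 5% as the arms converge, passing about 32% (36% at 300) for an assumed 20% on LPPSA and 15% on LISA. The relative reading and the two-sided alpha are assumptions where the article is silent, and the arm-specific rates are illustrations. That the paragraph names no arm, and that its assumed difference conflicts with the hypothesis, rests on the text alone.

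**What to change.** Revise the Sample size calculation and keep enrolment at 600:

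1. Name the arm to which each assumed BPD rate belongs, and say that the 25% is a historical planning rate not specific to LPPSA. The sponsor need not declare that LPPSA will have a different rate.
2. Remove the single 80% claim.
3. In line with the Background hypothesis, state the expected 95% confidence interval for the LPPSA minus LISA difference in BPD: half-width about 6 to 7.5 percentage points at 258 to 300 per group, for rates of 15% to 25%.
4. Add that a non-significant chi-squared test will not be read as showing non-inferiority. If a margin is specified in another trial document, cite it here with the power for that margin.

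The cost is one rewritten paragraph and a short precision table, with no extra infants. The downside is that the stated power becomes less favourable.

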### Randomization

A randomization sequence with 600 numbers (odd to even numbers in a 1:1 ratio) will be generated by a computerized random number generator and placed in sealed opaque envelopes. Infants with odd and even numbers will be assigned to the LISA and LPPSA groups, respectively. Twins or multiple birth infants will be randomized separately. Every eligible infant will be allocated to each group according to a randomized sequence within 30 min by an independent person (a nurse in Women’s Hospital School of Medicine, Zhejiang University).

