### Statistical methods

All data will be analyzed using SPSS version 20.0. To compare primary and secondary outcomes between the two groups, Student’s t-test (continuous variables) and the chi-squared test (categorical variables) will be used. The two-level hierarchical linear regression model or the logistic regression model, whichever is appropriate, will be applied for the comparison of the outcomes between the two groups, accounting for the infants’ characteristics, such as gestational age, birthweight, sex, appropriateness for gestational age, delivery mode, and pregnancy complications, and center variables, such as number of beds in the NICU and the number of infants with gestational age < 32 weeks. *P* < 0.05 will be regarded as statistically significant.

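### The 258 infants per group do not follow from a 25% BPD rate and a 20% reduction; if the reduction is relative and the test two-sided, power is about 27%, not 80%

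*Protocol article*

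**What the plan says.** All the inputs are in the protocol article, mostly under *Sample size calculation*. BPD alone drives the number. Two gestational-age strata are given BPD rates of about 60% and 15%, and these are combined: "The presumed incidence of BPD will be approximately 25% in the pooled population of our trial". The error rates follow ("Considering an alpha error rate of 0.05 and a power of 0.8"), then the target effect and the result: "a power of 0.8 to detect an expected 20% reduction in the incidence of BPD, 258 infants will be enrolled in each group". The recruitment target is 300 per group, to cover incomplete data and dropout. The section does not say whether the 20% is relative or absolute, whether the test is one- or two-sided, or which formula was used.

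Two other places bear on the calculation. *Randomization* fixes equal allocation ("odd to even numbers in a 1:1 ratio"). *Statistical methods* names the chi-squared test for categorical outcomes, with significance at P below 0.05.

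**The concern.** A comparison of two proportions with equal groups is fully determined by the two rates, alpha, sidedness and power. Apart from scale and sidedness, the protocol gives all of these. A fall from 25% to 20% is a small difference and normally needs about a thousand infants per arm, so 258 looks far too low. A fall from 25% to 5% is very large and needs only a few dozen, so on that reading 258 looks far too high.

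BPD is one of the primary outcomes and the only basis for the trial's size. If the statement stands, a result without a significant difference would be read as a trial with 80% power for a 20% reduction that found none. On the relative reading the trial would miss such an effect about 70% of the time. The risk of over-reading is greater here because *Background* states the hypothesis as LPPSA being not inferior to LISA, which invites a null comparison to be taken as evidence of similarity.

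**Working it through.** **Inputs.** Base rate p1 = 0.25, power 0.80, alpha 0.05 and n = 258 (300 with allowance for loss), all from *Sample size calculation*; 1:1 allocation from *Randomization*; chi-squared test from *Statistical methods*. Assumption: two-sided test, so z = 1.960 for alpha and 0.842 for power. The one-sided case (z = 1.645) is also shown.

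**Formula.** With p̄ = (p1 + p2)/2,

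n per group = [z_α √(2p̄(1−p̄)) + z_β √(p1(1−p1) + p2(1−p2))]² / (p1 − p2)²

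**Attempt to reproduce 258**

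- *Relative reading, 25% to 20%.* p̄ = 0.225. First term 1.960 × √0.34875 = 1.1575; second term 0.842 × √0.3475 = 0.4961. Then 1.6536² / 0.05² = 1,093.7, so **1,094 per group**.
- *Absolute reading, 25% to 5%.* p̄ = 0.15. First term 1.960 × √0.255 = 0.9897; second term 0.842 × √0.235 = 0.4080. Then 1.3977² / 0.20² = 48.8, so **49 per group**.

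Other standard formulas do not change this:

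| Comparison | Pooled | Continuity-corrected | Unpooled | Arcsine | One-sided, all four |
|---|---|---|---|---|---|
| 25% to 20% | 1,094 | 1,134 | 1,091 | 1,092 | 860–901 |
| 25% to 5% | 49 | 59 | 47 | 45 | 35–48 |
| 25% to 15% | 250 | 270 | 248 | 248 | 195–217 |

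The first two rows are the stated effect and neither contains 258. Taking 258 as half of a total (516) does not match either. The third row is not stated in the protocol; it is shown because it lies close to 258.

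**Power for the effect on the relative reading.** Power = Φ[(|p1 − p2| − z_α·SE0)/SE1], where SE0 = √(2p̄(1−p̄)/n) and SE1 = √((p1(1−p1) + p2(1−p2))/n).

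- n = 258: SE0 = 0.03677, SE1 = 0.03670. (0.05 − 1.960 × 0.03677)/0.03670 = −0.601, so power is **27.4%**.
- n = 300: SE0 = 0.03410, SE1 = 0.03403. (0.05 − 1.960 × 0.03410)/0.03403 = −0.494, so power is **31.1%**.
- One-sided 0.05: 38.8% at 258 and 42.9% at 300.

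**What 258 per group can detect.** Solving for p2 with p1 = 0.25 gives p2 = 15.1%, a fall of 9.9 points, or 9.9/25 = 39% relative. Power for 25% to 15% is 81% at 258 and 87% at 300.

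**How far the base rate would have to move.** For 258 per group to give 80% power for a 20% relative reduction, the base rate would have to be about 61%. That is above even the 60% quoted for the youngest stratum, while the pooled 25% implies that only (0.25 − 0.15)/(0.60 − 0.15) = 22% of infants are in that stratum.

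**Size of the shortfall.** 1,094/258 = 4.2. The step from 258 to 300 implies 1 − 258/300 = 14% loss. The same allowance applied to 1,094 gives 1,094/0.86 = 1,273 per group.

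**The case against.** The strongest objection is that the 27–31% power is conditional. The protocol labels neither scale nor sidedness; if the 20% is absolute, power exceeds 99.9% and the trial is overpowered, not underpowered. That is right as far as it goes, and the power figure should carry its assumption. But the absolute reading means an 80% relative fall, to 5% BPD, and needs about 49 per group, so 258 is then about five times too large. The stated number fails on both readings.

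The second objection is that 25% to 15% is reverse-engineered. The protocol names no 15% target (its 15% is the rate in the older stratum), and the scenario gives 250 or 270, not 258. Other unstated inputs come as close or closer: a one-sided 25% against 35% comparison gives 257–259, and non-inferiority with 25% in both arms, a margin of about 10.7 points and one-sided 0.025 gives 258. This stands in full as to origin: where 258 came from is unknown. It does not affect the statement of what 258 per group can detect, which is true whatever its source. Nor do these alternatives rescue the text, since the section gives no margin and describes detecting a reduction.

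Third, correcting the text at no cost presumes that the investigators accept the larger detectable effect. That also stands, and is carried into the fix. Finally, 31% assumes that all 300 are evaluable; on the plan's own allowance for loss the figure is 27%.

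**Conclusion.** The point holds. From the protocol's own inputs, 258 per group cannot be reproduced under either reading of the 20% reduction, with any of the usual formulas, one- or two-sided. Reading the reduction as relative and the test as two-sided, the required number is about 1,094 per group, and the trial has 27% power at 258 evaluable per group (31% at 300) against the stated 80%. Only the scale could change the direction of the error: on the absolute reading the trial is heavily overpowered, and 258 is still wrong. A one-sided test leaves power at 39–43%. With a 25% base rate, the trial is sized for a fall to about 15%, roughly twice the relative effect that the protocol names.

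**What to change.** Keep 600 infants and rewrite the sample size paragraph. Replace the 20% reduction wording with what the number supports, for example: 258 evaluable infants per group give about 80% power, at two-sided 0.05, to detect a fall in BPD from 25% to 15% (10 points absolute, 40% relative); power for a 20% relative reduction is about 27%. State both assumed rates, the scale, the sidedness and the formula. Carry the corrected detectable effect into the interpretation, so that a non-significant BPD comparison is not presented as excluding a 20% reduction or as showing non-inferiority.

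If the investigators can document how 258 was obtained, those inputs should be stated instead and checked against the hypothesis in *Background*.

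The cost is one paragraph and a less favourable stated effect. No infants are added, provided the investigators accept the larger detectable effect. If a 20% relative reduction is truly the target, the choice is between about 1,094 evaluable infants per group (1,273 recruited at the implied 14% loss) and openly stating the low power.

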### Intervention

Positive pressure with a T-piece system (Neopuff Infant Resuscitation®, Fisher and Paykel, Auckland, New Zealand) by a suitable mask will be applied to stabilize the infant after birth. Doctors in each participating center should be experienced using both methods. One must have experience with at least 10 cases implementing each technology.

#### LISA method

Oral sucrose will be encouraged during the whole procedure, and caffeine or any sedating drugs before operation will not be allowed in our trial. A specified thin catheter (1.67 mm in diameter and 150 mm long, designed by Shuanghe Pharmaceutical, Beijing) is inserted beyond the vocal cords to the required depth (25–27 weeks at 1 cm, 28–31 weeks at 1.5 cm) under direct vision by laryngoscopy. Surfactant will be administered through the thin catheter within 2–3 min. During the procedure, the infant will be on NCPAP with a PEEP of 6–8 cmH_2_O and will receive tactile stimulation by the operator or nurse, who will rub the back or flick the sole, to maintain spontaneous breathing during the whole surfactant administration. The catheter will be immediately withdrawn after surfactant administration. If the infant develops apnea, bradycardia, or desaturation, surfactant administration will be stopped immediately. If the condition does not improve in 30 s, a positive pressure ventilation will be given to recover the infants, as previously described [1, 6], and the case will be recorded as a failure of LISA.

#### LPPSA method

The same principle of premedication will be applied. Surfactant will be administered through an endotracheal tube under direct vision by laryngoscopy. Surfactant will be continuously administered through an endotracheal tube with mechanical ventilator or T-piece resuscitator. The initial setting will be as follows: PEEP of 6–8 cmH_2_O, peak inspiratory pressure of 12–15 cmH_2_O, and respiratory rate of 40 breaths per minute. If the infant develops apnea, bradycardia, or desaturation, surfactant administration will be stopped immediately. If the condition does not improve in 30 s, then conventional peak pressure ventilation (18–20 cmH_2_O or more), will be given, and the case will be considered as a failure case of LPPSA.

#### Surfactant dosage

Use of porcine surfactant (Curosurf®, Chiesi, Italy) or bovine surfactant (Calsurf®, Shuanghe, Pharmaceutical, Beijing) will be allowed in this trial. Based on literature concerned on the efficacy of different doses of surfactant and also from our experience, 200 mg/kg of porcine surfactant or 100 mg/kg of bovine surfactant will be used in the study. For infant with RDS as the primary cause, a second or third dose of 100 mg/kg (porcine) or 50 mg/kg (bovine) may be used if the infant’s condition is deteriorated and RDS is still the primary consideration.

#### CPAP and nasal intermittent positive-pressure ventilation (NIPPV)

Both CPAP and NIPPV may reduce the morbidity of BPD in preterm infants when they are used as primary respiratory support. However, no consensus exists on the optimal setting value. In the trial, we use NCPAP as the primary noninvasive respiratory support during and after surfactant administration. The initial setting of PEEP will be at least 6 cmH_2_O (6–8 cmH_2_O). Both constant and variant flow NCPAP equipment are permitted to use in the trial based on the individual requirement. The proximal end of the gastric tube will be kept open to avoid abdominal distension, and soothing care such as use of pacifier or chin fixer can be used to achieve the expected pressure.

